#### 3.6.2 Treatments Administered

The patients will receive 8700 U of rhBSSL or placebo, depending on the randomization schedule, added to each 100 mL of the food. The treatment will start on the day of randomization or the day after. The day of treatment initiation is defined as Day 1 (Baseline). Treatment will continue for 4 weeks, until the Day 29 body weight has been recorded.

### 3.6.3 Identity of Investigational Product

Recombinant human BSSL will be delivered as a sterile powder for oral solution, in a single-dose glass vial containing 8700 U (corresponding to 15 mg active rhBSSL). The content of 1 vial is intended for reconstitution in 1 mL of sterile water before addition to 100 mL of food. Each vial includes an overfill to ensure that 8700 U can be transferred to 100 mL of food. The matching placebo will also be delivered as a sterile powder for oral solution in an identical single-dose container.

Sobi will provide the study drug to PPD who will package and label the study drug before distributing it to the study centers.

[Table 3–2](#) presents the drug supplies that will be used in the study:

**Table 3–2 Study Drug Supplies**

| Product | Supplied as:                                      | Route |
|---------|---------------------------------------------------|-------|
| rhBSSL  | Sterile powder for oral solution
Sterile water | Oral  |
| Placebo | Sterile powder for oral solution
Sterile water | Oral  |

Abbreviation: rhBSSL, recombinant human bile-salt-stimulated lipase

The complete composition of rhBSSL drug product is presented in [Table 3–3](#).

**Table 3–3 Composition of rhBSSL Drug Product**

| Ingredient a | Quantity b | Function            |
|-------------------------|-----------------------|---------------------|
| rhBSSL                  | 8700 U/vial           | Active drug product |
| Sodium phosphate        | 1.8 mg/vial           | Buffer              |
| Sodium chloride         | 1.3 mg/vial           | Solubility          |
| Mannitol                | 43 mg/vial            | Bulking agent       |
| Glycine                 | 3.9 mg/vial           | Stabilizer          |

Abbreviation: rhBSSL, recombinant human bile-salt-stimulated lipase

a Placebo has the same composition as the active drug product except it does not contain rhBSSL.

b Each vial includes an overfill of 9% to ensure that 8700 U can be transferred to 100 mL of food.

### 3.6.4 Management of Clinical Supplies

#### 3.6.4.1 Study Drug Packaging and Storage

The study drug, rhBSSL and placebo, will be stored in single-dose glass vials fitted with rubber stopper and sealed with flip tear-off aluminum caps.

The vials are packed together with sterile water for reconstitution of the powder. 1-mL oral/enteral syringes intended for administration of the reconstituted medicinal product to the food and syringe tip caps will be provided. The syringes and tip caps will be provided sterile and individually packed for single use.

Recombinant human BSSL drug substance is manufactured by WuXi AppTec Inc, (Philadelphia, Pennsylvania, United States) and drug product and matching placebo are manufactured by Patheon Italia SpA (Monza, Italy). PPD Ireland is responsible for storage and distribution in Europe and the PPD depot in Russia is responsible for storage and distribution in Russia.

The study drug must be stored refrigerated at 2°C to 8°C at the study center in a secure area. Once the study drug has been mixed with the food it is stable for up to 30 hours if kept refrigerated at 2°C to 8°C in a secure location. However, instructions for use for the specific formula and the unit's normal procedure must be considered when maximum length of storage is determined if it is shorter than 30 hours.

Since BSSL is deactivated at higher temperatures, care should be taken if heating the final mixture of rhBSSL and food before administration. While heating, **the food temperature should not exceed 37°C**, and preferably a temperature-controlled water bath should be used.

#### 3.6.4.2 Preparation of Study Drug and Food

The pharmacist or delegate will mix the study drug with 1 mL of sterile water. If the reconstitution of study drug and the mixing of reconstituted study drug with the food is not done at the same location, the syringe can be transported with the tip cap in place. Each vial of study drug will be mixed with 100 mL of PBM or infant formula.

Each feeding should be drawn from the main food bottle, heated (**not above 37°C**) or given at room temperature, and the infant fed according to the unit's normal procedure. The main food bottle should not be heated and should remain refrigerated.

Additional details regarding the preparation of the food are provided in a separate study drug handling manual. Labels for rhBSSL have been designed according to regulatory and national requirements.

### **3.6.4.3 Study Drug Accountability**

The investigator will maintain accurate records of receipt of all study drug, including dates of receipt. In addition, accurate records will be kept regarding when and how much study drug is added to food. The amount of drug administered to the patients will be estimated from the food records ([Section 3.6.5.1](#)). All used study drug vials should be stored in a secure area for drug accountability (room temperature). At the completion of the study all remaining study drug will be reconciled and returned, or destroyed locally according to applicable regulations.

## **3.6.5 Food Requirements**

### **3.6.5.1 Daily Volume of Enteral Feeding**

Before inclusion of the first patient, each study center must determine a target food volume, to be used for all infants in the study. This volume should be in the range of 150 to 180 mL/kg/day. Once an infant has reached the target volume, the food volume should not be changed during the treatment period. Reasons for departure from the determined target volume must be recorded in the eCRF.

The daily volume (mL) of food enterally fed to the patient will be recorded in the eCRF every day during the treatment period ([Table 6–1](#)). The volume recorded should take into account the food that remained in the bottle at the end of feeding.

### **3.6.5.2 Daily Volume of Parenteral Nutrition**

The total daily volume (mL) of parenterally administered nutrition received by the patient during the treatment period will be recorded in the eCRF ([Table 6–1](#)). The product name and

volume of any parenterally administered nutrition containing a fat emulsion should also be recorded.

### 3.6.5.3 Infant Formula Requirements

Each study center will select one infant formula that all formula fed patients at that study center will be fed. They will remain on the same infant formula throughout the treatment period, unless medically contraindicated. The exact brand name of the infant formula used should be recorded in the eCRF to enable the composition to be derived.

The range of protein, carbohydrate, and lipid content for the infant formulas allowed for use in this study are

**Protein:** 2.8 to 4.1 g/100 kcal

**Carbohydrate:** 9.5 to 12.0 g/100 kcal

**Lipids:** 4.4 to 6.0 g/100 kcal

In addition, all infant formulas to be used in the study must contain AA and DHA. The infant formula must contain less than or equal to 40% of medium-chain TGs.

### 3.6.5.4 Pasteurized Breast Milk Requirements

There are no special requirements with regard to the source or quality of the PBM. The milk may be the mother's own or come from a milk bank (donor milk). Information about the predominant milk type will be recorded in the eCRF. The composition of the milk (fat, protein, and lactose) should be recorded when available. Fortification of the milk should be done according to a predefined study center-specific schedule. Preferably, one fortifier should be used at a study center, and the amounts added should be fixed, i.e., the same concentration added to all PBM. Fortification must not be individualized based on body weight. All use of fortifiers, including lipid emulsions, should be recorded in the eCRF.

The availability of PBM varies between NICUs, and thus the time period during which an infant is given only PBM before switching to infant formula will vary. In this study, the time of switching to infant formula must not be based on body weight. Instead, each study center

using PBM in this study should, before the first infant is randomized, declare which of the following alternatives will be followed for the infants in the study:

1. PBM only for 4 weeks
2. PBM only for 2 weeks followed by infant formula for 2 weeks

The date when infant formula is first introduced should be recorded in the eCRF, as well as the volumes of PBM and, if applicable, infant formula.

### **3.6.5.5 Concomitant Use of Fresh Breast Milk**

No fresh breast milk should be used during the 29 days of treatment. Any deviation from this rule must be noted in the eCRF. However, for ethical reasons, breast feeding cannot be prohibited. During the treatment period, the infants may be put to the breast, and the consumption of small volumes is allowed. If this is the case the date when fresh breast milk was first consumed will be recorded in the eCRF.

### **3.6.6 Blinding**

Recombinant human BSSL and placebo will be administered in a double-blind fashion. The randomization schedule will be maintained in a secure, locked location by PPD and will not be revealed to any study center personnel, investigators, sponsor personnel, PPD personnel, or the patient's legally acceptable representatives until after the database lock has been achieved. The PPD independent statistical team supporting the data safety monitoring board (DSMB) will have access to the randomization schedule ([Section 5.4](#)).

### **3.6.7 Breaking the Blind**

#### **3.6.7.1 Emergency Unblinding**

The PPD medical monitor will be responsible for maintaining the blind throughout the study. If a patient becomes seriously ill, the blind will be broken only if knowledge of the administered study drug will affect treatment options available to the patient.

At the initiation of the study, study centers will be instructed on the method for breaking the blind. This will be an electronic process via the IVRS, which is fully documented in the

IVRS manual. Blinding codes should only be broken in emergency situations for reasons of patient safety. The investigator should contact PPD, who will contact the sponsor before breaking the blind. In an emergency when there is insufficient time for the investigator to contact PPD or the sponsor, the investigator is permitted to break the blind without contacting PPD or the sponsor. The sponsor and PPD must be notified as soon as possible after the blind break. Only the IVRS user who is logged in during the emergency code break session will receive an unmasked copy of the notification in real time. All other users (clinical team and sponsor team) will receive a blinded real-time notification informing them of the code break.

### **3.6.7.2 Scheduled Unblinding**

The blind will be broken for an independent analysis and reporting team within PPD and for Sobi once the last patient has completed the 3-month visit and 200 patients have completed the 12-months-corrected-age visit, including the Bayley assessment. Once unblinding has occurred, the unblinded teams will not be involved in decisions regarding individual patients where the patient identity can be revealed. The blind will be maintained for all other teams within PPD, personnel at the sites, and the patients' legally authorized representatives until the end of the study. For details of study reporting, see [Section 5.8](#).

### **3.6.8 Treatment Compliance**

Measures of treatment compliance are not applicable for this study.

### **3.6.9 Prior, Concomitant, and Subsequent Therapy**

Other therapy considered necessary for the patient's welfare may be given at the discretion of the investigator. All such therapy must be recorded in the eCRF. The patient is not allowed to participate concurrently in another clinical intervention study and as such may not use any drug or treatment concurrently under investigation until the patient has completed the 12-months-corrected-age visit.

Preterm infants often experience complications that need therapeutic intervention. This can in most cases be accepted as long as the medication does not interfere with feeding.

All use of concomitant and subsequent medications, from the start of the study up to the 3-months follow-up visit, will be recorded in the patient's eCRF ([Table 6–1](#) and [Table 6–2](#)). This will include all prescription drugs, herbal products, vitamins, minerals, and over-the-counter medications. Any changes in concomitant medications also will be recorded in the patient's eCRF.

### **3.7 Statistical Analysis Plan**

A detailed statistical analysis plan will be prepared for this study before the clinical database is locked and should be referred to for further details of the statistical analysis.

#### **3.7.1 Primary Efficacy Endpoints**

The primary efficacy variable is growth velocity in grams per kilogram per day during 4 weeks of treatment.

#### **3.7.2 Secondary Efficacy Endpoints**

In addition to the primary efficacy endpoint, the following secondary efficacy endpoints will be evaluated to support the primary objective:

- Change from Baseline in body weight (g) at 3 months
- Body weight (g) at 12 months corrected age
- Change from Baseline in total body length (mm) at 4 weeks and 3 months
- Body length (mm) at 12 months corrected age

The following secondary efficacy endpoint will be evaluated to support the objective “To determine the effect of rhBSSL treatment in decreasing risk of growth restriction”:

- Growth restriction, defined as growth velocity <15 g per kilogram bodyweight per day during 4 weeks of treatment

The following secondary efficacy endpoints will be evaluated to support the objective “To determine the effect of rhBSSL treatment in shortening the time of hospital stay”:

- Time to readiness for discharge. This endpoint will be defined as the time from Baseline when all of the following criteria have been fulfilled: a sustained weight gain, ability to maintain normal body temperature, ability to suckle feed, and ability to maintain stable cardiorespiratory function.
- Time to discharge

The following secondary efficacy endpoints will be evaluated to support the objective “To determine the effect of rhBSSL treatment in improving early development”:

- Change from Baseline in head circumference (mm) at 4 weeks and 3 months
- Head circumference (mm) at 12 months corrected age
- Time from Baseline to 150 mL/kg/day of enteral feeding

The following secondary efficacy endpoint will be evaluated to support the objective “To determine the effect of rhBSSL treatment on decreasing readmittance to hospital”:

- Readmission to hospital within 1 month of discharge

The following secondary efficacy endpoints will be evaluated to support the objective “To determine the effect of rhBSSL treatment on increasing the levels of DHA and AA”:

- Levels of DHA and AA at 4 weeks

The following secondary efficacy endpoints will be evaluated to support the objective “To determine the effect of rhBSSL treatment on neurodevelopment”:

- Bayley-III scores at 24 months corrected age
  - Cognitive domain composite score
  - Language domain composite score
  - Motor domain composite score
  - Social-emotional domain composite score
  - Adaptive domain composite score

- Scaled scores for each subtest and for the cognitive and social-emotional domains (in total 16 scaled scores)
- Neurodevelopment disability composite at 24 months corrected age (as defined in [section 3.4.3.9](#))
- CBCL scores at 24 months corrected age
  - Scores for each of 7 syndrome sub-scales (emotionally reactive, anxious/depressed, somatic complaints, withdrawn, sleep problems, attention problems and aggressive behavior)
  - Score for internalizing problems
  - Score for externalizing problems
  - Score for total problems

The following secondary efficacy endpoints will be evaluated to support the objective “To determine the long-term effect of rhBSSL treatment on anthropometrics”:

- Body weight (g) at 24 months corrected age
- Body height (cm) at 24 months corrected age
- Head circumference (mm) at 24 months corrected age

### 3.7.3 Safety Endpoints

The study has the following secondary safety endpoints to meet the objective “To compare the safety and tolerability of rhBSSL treatment in preterm infants with that of placebo treatment after oral administration in infant formula or PBM”:

- AEs up to 3 months and SAEs up to 12 months corrected age
- Bayley-III scores at 12 months corrected age
  - Cognitive domain composite score
  - Language domain composite score
  - Motor domain composite score

- Scaled scores for each subtest and for the cognitive domain (in total 5 scaled scores)
- Vomiting (frequency and volume)
- Vital signs (heart rate, blood pressure, body temperature)
- Levels of amylase, bilirubin, aminotransferases, sodium, and urea
- Levels of vitamins A and D
- Presence of rhBSSL antibodies

The study has the following secondary safety endpoints to meet the objective “To determine the long-term safety of rhBSSL treatment”:

- Serious ADRs up to 24 months corrected age

### **3.7.4 Health Economic Endpoints**

The study has the following health economic endpoints to meet the objective “To assess the effect of rhBSSL treatment on health care utilization”:

- The number of outpatient visits from the time of initial hospital discharge to home up to 24 months corrected age
- The number of inpatient visits, days of hospitalization and days in intensive care unit from the time of initial hospital discharge to home up to 24 months corrected age

The study has the following endpoint to meet the objective “To assess the effect of rhBSSL treatment on indirect resource use”:

- Number of days lost from work related to the child’s condition from the time of initial hospital discharge to home up to 24 months corrected age

The study has the following endpoint to meet the objective “To assess the effect of rhBSSL treatment on chronic medical conditions/diagnoses”:

- Presence of chronic medical conditions/diagnoses at 24 months corrected age

### 3.7.5 Exploratory Endpoints

The study has the following exploratory endpoints:

- Levels of fatty acids
- Percent body fat
- Fecal calprotectin concentration
- Fecal microbiota

### 3.7.6 Sample Size Calculations

Assuming a true difference in growth velocity between rhBSSL and placebo of 2.25 g/kg/day at 4 weeks and a standard deviation of 7 g/kg/day, 205 evaluable patients in each treatment arm provide 90% power to demonstrate that rhBSSL improves growth velocity compared with placebo (using a 2-sided test with a significance level of 5%). Allowing for 5% of patients to be excluded from the FAS, it is estimated that 432 patients will be randomized. These assumptions are based on the meta-analysis of Sobi's 2 previous Phase 2 studies; the estimate of standard deviation has been increased by 30% to allow for greater variability within the Phase 3 study population.

The sample size calculation was performed using nQuery Advisor software Version 4.0 (Statistical Solutions, Ltd, Cork, Ireland).

### 3.7.7 Analysis Sets

The following analysis sets will be used in the statistical analyses.

Full-analysis set: The FAS is the primary analysis set and will consist of all patients randomly assigned to treatment who have a baseline and at least 1 postbaseline assessment of body weight. All analyses using the FAS will group patients according to randomized treatment.

Per-protocol set (PPS): The PPS is the secondary analysis set and will consist of all FAS patients who receive the treatment according to randomization, have no major protocol violations, and remain in the study for a minimum of 1 week. Further criteria may be specified in the statistical analysis plan.

Safety set: The safety set will consist of all patients who received at least 1 dose of study drug. All analyses using the safety set will group patients according to treatment actually received.

The FAS will be used as the primary population and the PPS as supportive for the analyses of the primary efficacy variable, the FAS will be used for the secondary efficacy variables, and the safety set will be used for the safety analysis.

### 3.8 Statistical Analysis

Demographic data and background characteristics will be summarized using descriptive statistics. Continuous variables will be summarized using the mean, the standard error of the mean, the median, the minimum value, and the maximum value. Categorical variables will be summarized using frequency counts and percentages. All data will be listed in data listings.

Details of all analyses will be described in the statistical analysis plan.

Statistical analysis will be performed using SAS software Version 9.1 or later (SAS Institute, Inc, Cary, North Carolina, United States). All statistical tests will be 2-sided and performed using a 5% significance level, leading to 95% (2-sided) confidence intervals.

#### 3.8.1 Primary Efficacy Analysis

The null and alternative hypotheses are defined for the primary efficacy variable (growth velocity during the 4 weeks of treatment):

$$H_0: \mu_{\text{rhBSSL}} = \mu_{\text{placebo}}$$

$$H_A: \mu_{\text{rhBSSL}} \neq \mu_{\text{placebo}}$$

In order to calculate growth velocity, the natural log-transformed value of the baseline and all postbaseline weight assessment for each patient will be calculated. A linear regression model will then be fitted for each patient with a response variable of log(weight) and a predictor variable of time. Growth velocity for each patient will be estimated as the slope arising from the regression model, and will need to be multiplied by 1000 for conversion into the desired unit of grams per kilogram per day. The weight over time for each treatment group will be

illustrated graphically and if the log-transformed data clearly deviate from the linearity assumption, a sensitivity analysis will be performed using untransformed data.

Statistical analysis for the primary efficacy variable will be performed using an analysis of covariance model including factors for treatment, feeding regimen (PBM or infant formula), size for gestational age category (SGA or AGA), with baseline weight included as a covariate. For the comparison between treatment groups, the point estimate and the associated 95% confidence interval and *P* value from the model will be presented.

The assumptions of normality and homogeneity of variance will be assessed by inspection of normal probability plots and residual plots. If either assumption is clearly not met, a corresponding nonparametric analysis will be performed (using the same analysis of covariance model, but using ranked response and covariate) to check the robustness of the results.

It is anticipated that the withdrawal rate from the study after randomization will be approximately 15%. For the primary analysis, if patients withdraw before 4 weeks then growth velocity will be derived using weight assessments up to their last available assessment. Sensitivity analyses will be conducted to assess the impact of missing data.

The methods for handling of missing data will be fully described in the SAP.

The primary efficacy variable will be analyzed using both the FAS (the primary population for efficacy evaluation) and PPS (supportive).

### **3.8.2 Secondary Efficacy Analyses**

The secondary efficacy variables will be analyzed using the FAS only.

The following will be analyzed using an analysis of covariance approach similar to that used for the primary endpoint. No logarithmic transformation will be performed for these endpoints.

- Change from Baseline in body weight (g) at 3 months,
- Body weight (g) at 12 months corrected age,

- Change from Baseline in total body length (mm) at 4 weeks and 3 months,
- Body length (mm) at 12 months corrected age,
- Change from Baseline in head circumference (mm) at 4 weeks and 3 months,
- Head circumference (mm) at 12 months corrected age

The following will be analyzed using descriptive statistics:

- Body weight (g) at 24 months corrected age
- Body height (cm) at 24 months corrected age
- Head circumference (mm) at 24 months corrected age
- Weight-to-length ratio (g/cm) at 4 weeks

The growth restriction is defined as a growth velocity of less than 15 g per kilogram bodyweight per day during the 4-week treatment period and will be analyzed using a logistic regression model with treatment, feeding regimen (PBM or infant formula), and size for gestational age category (SGA/AGA) as explanatory variables. Based on this model, the estimated risk of growth restriction in the rhBSSL and placebo groups respectively, the estimated odds ratio, the associated 95% confidence interval and P-value will be presented. If the risk of growth restriction in the rhBSSL group is statistically significantly lower than in the placebo group, it will be concluded that rhBSSL reduces the risk of growth restriction in preterm infants receiving infant formula or PBM. In addition, the number and proportion of patients in each treatment group with growth restriction will be presented for all patients as well as by feeding regimen and by size for gestational age category.

Time to readiness for discharge will be analyzed using an analysis of variance model. Time to readiness for discharge will be used as the response variable and factors will be included for treatment, feeding regimen (PBM or infant formula) and size for gestational age category (SGA or AGA). For the comparison between treatment groups, the point estimate, the associated 95% confidence interval and P-value from the model will be presented.

Time to discharge will be analyzed using an analysis of variance model similar to that used for time to readiness for discharge.

Readmission to hospital within 1 month of discharge will be analyzed using a logistic regression model with treatment, feeding regimen (PBM or infant formula), and size for gestational age (SGA/AGA) as explanatory variables. Based on this model, the estimated risk of readmission to hospital in the rhBSSL and placebo groups respectively, the estimated odds ratio and the associated 95% confidence interval will be presented. In addition, the number and proportion of patients in each treatment group who were readmitted to hospital will be presented for all patients as well as by feeding regimen and by size for gestational age category.

Time from start of treatment to 150 mL/kg/day of enteral feeding will be presented using descriptive statistics.

Statistical analysis of the Bayley-III cognition, language, motor, social-emotional and adaptive behavior composite scores at 24 months corrected age will be performed using an analysis of covariance model including factors for treatment, feeding regimen (PBM or infant formula), size for gestational age category (SGA or AGA), and critical confounders for neurodevelopment included as covariates. Based on this model, the estimated mean score for each treatment group, the estimated difference between treatments and the associated 95% confidence interval will be presented. The critical confounders to be included in the model will be specified in a study-specific statistical analysis plan finalized prior to breaking the blind. In addition, the respective domain composite score and the scaled score for each subtest at 24 months corrected age will be presented by descriptive statistics.

The neurodevelopment disability composite outcome will be analyzed using a logistic regression model including treatment, feeding regimen (PBM or infant formula), size for gestational age category (SGA or AGA) and critical confounders for neurodevelopment included as explanatory variables. Based on this model, the estimated risk of a neurodevelopment disability in each treatment group, the estimated odds ratio for rhBSSL to placebo and the associated 95% confidence interval will be presented. The critical confounders to be included in the model will be specified in a study-specific statistical analysis plan finalized prior to breaking the blind. Furthermore, the number and proportion of patients in each treatment group with a neurodevelopment disability (according to the above

scale) will be presented for all patients as well as by feeding regimen and by size for gestational age category. This latter presentation will also be done for each individual component of the composite for all patients and by feeding regimen and by size for gestational age category.

The CBCL scores will be analyzed using descriptive statistics.

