#### **3.4.3.2 Total Body Length**

During the treatment period, the patient's total length (mm) will be measured from the crown to the heel using a preterm infant length board provided for the study and recorded in the eCRF. Preferably and where possible the same equipment should also be used for assessments made after the treatment period. Total body length should be measured according to separate detailed instructions. This measurement should be made at Baseline (Day 1), Days 8, 15, 22, and 29, at discharge, and at the 3-months and the 12-months-

corrected-age follow-up visits ([Table 6–1](#) and [Table 6–2](#)). Measurements up to discharge should be taken as near to the same time each day as is possible.

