### 3.6 Study Treatments

#### 3.6.1 Method of Assigning Patients to Treatment Groups

Patients will be randomly assigned to receive either rhBSSL or placebo.

An interactive voice recognition system (IVRS) will be used for the randomization. Biostatistics will generate the randomization schedule for IVRS, which will link sequential patient randomization numbers to treatment codes. The randomization will be stratified by feeding regimen (PBM or infant formula) and by size for gestational age category (SGA or AGA). An infant having a birth weight that lies above the 10th percentile for the gestational age on the gender-specific intrauterine growth curves presented by [Olsen et al 2010](#) is defined as AGA. An infant with a birth weight at or below the 10th percentile is defined as SGA. In this study at least 10% of the infants will be SGA at birth and at least 15% of the infants will be fed with PBM.

The randomization numbers will be blocked, and within each block the same number of patients will be allocated to each treatment group. The block size will not be revealed.

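### The 4-week length and head circumference endpoints rest on the Day 29 reading alone; the scheduled Day 8, 15 and 22 readings have no analytic role, and the primary analysis's rule for early withdrawals cannot be carried over

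*Protocol*

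**What the plan says.** Protocol 3.8.2 lists "Change from Baseline in total body length (mm) at 4 weeks and 3 months" and "Change from Baseline in head circumference (mm) at 4 weeks and 3 months" among the endpoints analysed by an ANCOVA like that of the primary endpoint, without log transformation and in the FAS only. The Statistical Methods part of the Synopsis says the same.

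The readings are more frequent than that analysis needs. For length, 3.4.3.2 states: "This measurement should be made at Baseline (Day 1), Days 8, 15, 22, and 29, at discharge". Section 3.4.3.4 sets the same days for head circumference. No section gives the Day 8, 15 and 22 values of either measure a role in the analysis.

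For weight, 3.8.1 fits a slope to the baseline and all later log weights. Infants who leave before 4 weeks are analysed on the weights they have, and the sentence limits this rule to the primary analysis. The same section says: "It is anticipated that the withdrawal rate from the study after randomization will be approximately 15" percent. It leaves missing-data methods to the SAP, and 3.8 leaves the details of all analyses there.

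Under 3.7.7 the FAS needs a baseline and one later body weight. It does not need a length or head circumference reading at any visit.

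**The concern.** A slope can be estimated from a shortened series of weights. A change at 4 weeks cannot be formed without a 4-week value. The rule that keeps early withdrawals in the primary analysis therefore has no counterpart here. Carrying a Day 8 length forward would not supply one, because it would record about one week of growth as four.

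As 3.8.2 is worded, an infant with readings on Days 8, 15 and 22 but none on Day 29 belongs to the analysis set and contributes nothing to the model, unless a value is imputed. Information already collected on that infant is then unused. If infants without a Day 29 reading grow differently from the rest, the comparison also shifts towards a selected group.

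These are not marginal endpoints: 3.7.2 attaches length to the primary growth objective and head circumference to the early-development objective.

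**Working it through.** **The plan's own figure.** Section 3.7.6 holds the only power statement in the protocol: "205 evaluable patients in each treatment arm provide 90% power to demonstrate that rhBSSL improves growth velocity compared with placebo". Its inputs are δ = 2.25 and SD = 7 g/kg/day, with two-sided α = 0.05. Allocation is equal, since "within each block the same number of patients will be allocated to each treatment group" (3.6.1).

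- n per arm = 2(1.960 + 1.282)² × 7² / 2.25² = 203.4, so 204 by the normal approximation. A noncentral t calculation gives 205 (power 0.9009; 0.8995 at 204).
- 410 / 0.95 = 431.6, so 432 randomized.

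The stated figures reproduce. They concern growth velocity only. The protocol gives no SD, effect or power for length or head circumference, so both calculations below are illustrations.

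**Calculation A: standardised effect borrowed from the primary endpoint.** δ = 2.25 / 7 = 0.321, 205 per arm, power = Φ(δ√(nf/2) − 1.96), where f is the effective fraction of the sample.

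- Complete Day 29 data: 0.321 × √(205/2) = 3.254; Φ(1.294) = 90.2%.
- 15% without Day 29, ANCOVA on the rest, f = 0.85: 0.321 × √(174.25/2) = 3.000; Φ(1.040) = 85.1%.

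For the repeated-measures model, let Σ be the covariance of the change at Days 8, 15, 22 and 29, and let p_k be the share of infants observed for the first k visits only. The information on the visit means is the sum over k of p_k Σ_k⁻¹, with Σ_k the leading k × k block of Σ and the block filled out with zeros. With unit variances, f is the reciprocal of the Day 29 element of the inverse of that sum. Assumptions: random loss spread evenly over the four weeks (a quarter of it before Day 8), and correlation 0.5 to 0.9 with compound-symmetry or AR(1) structure. Gains are taken before rounding.

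| Without Day 29 | Day 29 ANCOVA | f, repeated measures | Power, repeated measures | Gain (points) |
|---|---|---|---|---|
| 5% | 88.7% | 0.954–0.981 | 88.8–89.7% | 0.1–1.0 |
| 10% | 87.0% | 0.908–0.963 | 87.3–89.1% | 0.3–2.1 |
| 15% | 85.1% | 0.862–0.943 | 85.6–88.5% | 0.5–3.4 |

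**Calculation B: effect set to 80% power with complete data.** δ = (1.960 + 0.842) × √(2/205) = 0.277. Assumed: true baseline SD 4, true 4-week change SD 1, measurement-error SD 0.3, 0.5 or 1.0, baseline value adjusted for, known covariance, and last reading of those lost spread evenly over Days 8, 15 and 22.

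- 15% lost, Day 29 ANCOVA: 0.277 × √(174.25/2) = 2.583; Φ(0.623) = 73.3%.
- 15% lost, visit-as-category model: 77.7%, 76.7% and 75.7% for the three error SDs, a gain of 4.4, 3.4 and 2.4 points.
- 5% lost: a gain of 1.3, 1.0 and 0.7 points.

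Taken together, the gain is about 0.5 to 4.4 points at 15% and 0.1 to 1.3 points at 5%.

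**What linearity adds.** A random-slope model on all five readings shows a larger gain at 15% loss in simulation under B, about 5 to 7 points. With no loss at all, however, the same model reaches 81.2%, 82.6% and 85.1% against the 80% benchmark. Part of its gain therefore comes from imposing linear growth, which the simulation makes true, and not from retaining early withdrawals.

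**The case against.** **The SAP may settle it.** Missing-data methods and analysis details are deferred to the SAP, which is not at hand. A reader might infer from 3.8.2 that infants without a Day 29 value are excluded. The protocol does not say so, and the FAS definition keeps them in the set. This stands, and it is why the point is worded as no contribution unless a value is imputed. What remains is that the single-time-point model is fixed in the protocol itself, so a longitudinal model would depart from 3.8.2 as written.

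**The 15% is not loss before Day 29.** A reader might apply it that way. It is withdrawal from the whole study, which has follow-up to 12 and 24 months corrected age. Section 3.2.2 also excludes infants expected to stay less than 4 weeks, so Day 29 is planned as an inpatient reading. This stands: 15% marks the upper end, and the share before Day 29 is not given.

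**The ANCOVA is a standard analysis.** It fits the endpoint as defined, and nothing in 3.8.2 is contradictory. This also stands; the point is an efficiency improvement, not an error. Nor is the mixed model free of assumptions. For an infant who dies before Day 29 it implies a Day 29 value under missing-at-random, which is open to question.

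**Bias.** A reader might infer that the infants who leave are the slower growers and that the result is therefore biased. That is plausible, but the protocol has no data on it, and nothing here puts a size or direction on it.

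**Conclusion.** The point holds as a low-cost improvement of minor weight. Section 3.8.2 fixes a Day 29 ANCOVA, leaves three scheduled readings per infant without a use, and cannot borrow the primary analysis's treatment of early withdrawals. A repeated-measures model does better in every scenario examined, but not by much: about 0.5 to 4.4 power points if 15% lack a Day 29 reading, and about 0.1 to 1.3 points at 5%. These figures depend on assumed effects, correlations and loss patterns, and on loss at random. An infant with no reading after Day 1 stays uninformative under either method. A claim of 5 to 7 points is not supported as the value of retaining early withdrawals, because it leans on linear growth in length and head circumference, which the protocol does not establish.

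**What to change.** In 3.8.2, and in the matching Synopsis text, analyse the 4-week change in length and in head circumference with a repeated-measures mixed model in the FAS:

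- response: change from Baseline at Days 8, 15, 22 and 29;
- terms: visit as a category, treatment, treatment-by-visit, feeding regimen, SGA/AGA, baseline weight and the baseline value of the measure;
- unstructured within-infant covariance;
- result: the treatment difference at Day 29 with its 95% confidence interval.

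Keep the Day 29 ANCOVA as a sensitivity analysis. The 3-month and 12-month analyses need no change.

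The cost is a wording change and modest programming. All readings are already scheduled, so no new data are needed. The price in assumptions is reliance on missing-at-random; linear growth is not required.
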